#### Moderation and mediation analysis

The moderating effect of the socio-demographics (age, gender, education, working situation, family situation) and disease-related characteristics of the patients (type of cancer, stage of disease, duration and treatment of cancer) on the effectiveness of the intervention will be analyzed using regression analyses.

Mediation analysis will be performed as described by Preacher and Hayes [52,53]. Aim of this analysis is to assess whether psychological flexibility, self-compassion, supportive behavior, posttraumatic growth and resilience are mediators in the effect between the independent variable and the dependent variables.

### Sample size calculation

Based upon a previous, similar study [54] we expect effect sizes of at least d = 0.5. To demonstrate the presence of an effect of at least d = 0.5 as statistically significant in a two-tailed test at alpha = 0.05 and a power of (1-beta) = 0.80, a minimum of 64 participants in each condition will be required at follow-up (power calculation in G*Power). We have extended our sample size with 5 participants per condition in order to take normal distribution of the data as well as possible post hoc tests into account. Anticipating a drop-out rate of 20% between T0-measurement and T3-measurement, at least 87 participants per condition need to be included at T0-measurement. The total study cohort comprises thus 261 participants.

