### Present study

This present study has several aims. First, we want to assess the (cost-)effectiveness of the intervention *Hold on, for each other*. Our main hypothesis is that both versions of the intervention lead to a significant reduction of psychological distress compared to a waiting list control condition. In addition, we hypothesize that (positive) mental health, health related quality of life and general health of participants of the experimental conditions will increase and caregiver burden will decrease in comparison to the participants in the waiting list control condition. The second aim of our study is to examine if psychological flexibility, self-compassion, mastery, style of support behavior (overprotection, protective buffering, active engagement), posttraumatic growth and resilience are mediators of the intervention’s effects on the partners’ mental health. Third, we aim to examine the moderating effects of the socio demographics (age, gender, education, working situation, family situation) and disease-related characteristics of the patients (sort of cancer, stage of disease, duration and treatment of cancer). Finally, we want to know to what extend participants are satisfied with the intervention, which parts of the intervention are mostly used, and how compliant the users are.

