#### Effects

One-way ANOVA’s and χ^2^-tests will be performed to see if there are no significant differences at baseline between the two conditions for any of the demographic variables or outcome measures. Non-significant differences will indicate successful randomization. Intention-to-treat analyses will be conducted with use of SPSS missing values analysis to impute all missing data on the continuous measuring multiple imputation methods in SPSS. To examine differences between the conditions on all outcome measures, ANOVA (group x time) will be used. In the case of significant group x time – interactions, Tukey’s post hoc tests will be used.

Effect sizes on the primary outcome variable (HADS total) at post-intervention will be calculated with Cohen’s D using the means and pooled standard deviations of the measurements of the conditions (effect size of above .56 are considered large, .33-.55 are considered moderate, and less than .33 are considered as small [51].

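### The 5 extra participants per arm do not cover the planned Tukey tests: at 69 per arm and d = 0.5, power on post-intervention scores is about 72% per comparison, and 80% would need 83 per arm

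*Protocol article*

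**What the plan says.** Sample size calculation: the authors write that "we expect effect sizes of at least d = 0.5". They size for this effect being "statistically significant in a two-tailed test at alpha = 0.05" with "a power of (1-beta) = 0.80", and conclude that "a minimum of 64 participants in each condition will be required at follow-up". They then add an allowance: "We have extended our sample size with 5 participants per condition in order to take normal distribution of the data", and the same sentence gives possible post hoc tests as a further reason. No calculation is shown for the 5. With 20% drop-out between T0 and T3, the 69 becomes 87 per condition and 261 in total.

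Statistical analysis, Effects: outcomes are compared by a group x time ANOVA and, if the interaction is significant, "Tukey’s post hoc tests will be used". Cohen's d for the HADS total is computed from post-intervention means and pooled standard deviations.

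Present study: the main hypothesis is that "both versions of the intervention lead to a significant reduction of psychological distress compared to a waiting list control condition".

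Study design and Randomization: the waiting list is offered the intervention directly after the three-month measurement (T1).

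**The concern.** The 64 per arm belongs to a single two-group comparison at two-sided 0.05. Tukey's test over three arms uses a stricter critical value for each pair, so the same sample gives less power. The article says that the 5 extra participants allow for this, which is a claim that can be checked. The main hypothesis also involves two comparisons with the waiting list, and no power is given for succeeding on both.

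What is at stake is the chance of missing a real effect of the planned size. The design accepts a 20% chance of a miss. If the allowance is too small, the true chance per comparison is higher, and a reader of the sample size section would not know it.

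**Working it through.** **Inputs.** From Sample size calculation: d = 0.5, two-sided alpha 0.05, power 0.80, 64 per arm, plus 5, drop-out 20%. From Study design: three parallel arms (equal sizes follow from 3 × 87 = 261). From Effects: Tukey's test, with d on post-intervention means and pooled SD.

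**Step 1: the article's own figures.** The two-sample t-test (noncentral t) at d = 0.5 and 80% power needs n = 63.77, so 64 per arm (power 80.1%). Then 64 + 5 = 69; 69/0.80 = 86.25, so 87; 3 × 87 = 261. All reproduce. At 69 per arm the unadjusted test has 83.0% power.

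**Step 2: Tukey, one comparison, post-intervention scores.** The critical |t| is q(0.95; 3, df)/√2 with df = 3(n − 1). At n = 69, df = 204 and the critical value is 2.361, which is a two-sided level of about 0.019. The unadjusted value is 1.972. The noncentrality is d√(n/2) = 0.5 × √34.5 = 2.937.

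| n per arm | Tukey power, one comparison |
|---|---|
| 64 | 67.9% |
| 69 | 71.7% |
| 82 | 79.98% |
| 83 | 80.5% |
| 87 | 82.6% |

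So 80% needs 83 per arm at follow-up, and 83 − 64 = 19. Requiring a significant omnibus F first changes the 71.7% only to 71.4%.

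**Step 3: two comparisons sharing one control arm.** Simulation of 2,000,000 trials, pooled variance, both true effects d = 0.5, 69 per arm, Tukey: both significant 57.9%, at least one 85.5%. Without any adjustment, both are significant in 73.3%. Part of the shortfall for the joint claim therefore comes from needing two successes and not from Tukey.

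**Step 4: how many contribute at T1.** The 69 is what remains after the loss planned up to T3, but the waiting list is a control only up to T1. Loss by T1 is not stated, so I take 69 to 87 as the range.

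| n per arm at T1 | One comparison | Both |
|---|---|---|
| 69 | 72% | 58% |
| 78 | 78% | 66% |
| 87 | 83% | 72% |

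**Step 5: change scores instead of post scores.** For change from baseline, the effective effect is 0.5/√(2(1 − r)), where r is the pre-post correlation. The article gives no r, so the values below are assumptions. At 69 per arm, Tukey:

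| Assumed r | Effective d | One comparison | Both |
|---|---|---|---|
| 0.3 | 0.423 | 55% | 38% |
| 0.5 | 0.500 | 72% | 58% |
| 0.6 | 0.559 | 82% | 72% |
| 0.7 | 0.645 | 92% | 87% |

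**Step 6: alternatives at 69 per arm, post scores (same simulation).** Three-arm omnibus test followed by unadjusted pairwise contrasts: 79.5% each, 72.7% both. Hochberg on the two contrasts with the waiting list: 81.1% each, 73.2% both.

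**The case against.** The case for the plan has several parts, and much of it stands.

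- *The arithmetic is right.* The 64, 69, 87 and 261 all reproduce, and the 80% is attached to a single two-tailed test, for which it is true. A reader might infer a calculation error. There is none. The fault is a mismatch between the sample size and the planned test.
- *More than 69 per arm may be available at T1.* This stands. With 83 or more, Tukey reaches 80% per comparison. But the article sets its own requirement at 69 after loss, and even with all 87 the joint figure is 72%.
- *The planned analysis is group x time, which may gain from the baseline measurement.* This stands as a qualification. The gain depends on a correlation that the article does not give, and at a low correlation it becomes a loss. It cannot support the stated 80%.
- *Both versions need not mean that both comparisons must succeed.* The hypothesis can also be read as two separate claims, one per version. The 58% therefore belongs to one reading, and the figure for at least one is about 86%.
- *Tukey is a valid choice.* The description of the intervention states an interest in comparing the two kinds of support, so controlling all three pairs is defensible.

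A reader might also infer that Tukey would compare arm means averaged over visits, baseline included, which would cut power sharply. The article does not say which means Tukey compares. It makes the test follow a significant group x time interaction, which points to differences over time. That reading would rest on assumed software behaviour, and it is no part of this point.

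**Conclusion.** The concern holds in a limited form. On the article's own basis (d = 0.5 on post-intervention scores, 69 analysed per arm, Tukey over three arms), the chance of missing a real effect is about 28% per comparison (100 − 71.7), against the 20% accepted. The 5 extra participants cover only part of the 19 that Tukey alone would take, and they are also meant to cover the distribution of the data.

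If both comparisons must succeed, the chance of failure is about 42% (100 − 57.9). That figure rests on this reading of the hypothesis and on both true effects being 0.5.

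It would go too far to say that the trial simply has 72% and 58% power. Depending on attendance at T1, the figures run to 83% and 72%. On change scores they could be lower or higher. Control of false positive findings is not affected. What needs correcting is the power statement.

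**What to change.** **Needed, without enrolling more.** In Sample size calculation, state power for the test, time point and number of comparisons actually planned. For Tukey on post-intervention scores with 69 per arm, that is about 72% per comparison and 58% for both versions. If T1 is named as the time point, give the expected number at T1. If change scores are used, give the assumed correlation and a range. Remove the statement that the 5 extra per condition take post hoc tests into account. The cost is wording only, and the stated power becomes less favourable.

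**Optional.** Name the two contrasts with the waiting list at T1 as primary. Test them by the three-arm omnibus test at 0.05 followed by unadjusted pairwise contrasts, which controls the family-wise error with three arms (just under 80% each, 73% both at 69 per arm), or by Hochberg (81% each, 73% both). Report personal versus automated support as an estimate with a 95% confidence interval. The drawback is that this comparison loses its confirmatory test, and the joint claim still falls short of 80% at 69 per arm. Keeping Tukey with restated power is equally valid.

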## Discussion

*Hold on, for each other* is the first web-based self-help intervention for partners of cancer patients that is based on both a clear theoretical framework and an iterative and user-centered development. The main purpose of the RCT is to evaluate the (cost-)effectiveness of *Hold on, for each other*, a recently developed web-based intervention for partners of cancer patients. Additional goals are: (1) to examine if psychological flexibility, self-compassion, mastery, supportive behavior, posttraumatic growth and resilience are mediators of the intervention’s effects on the partners’ mental health; (2) to examine the moderating effects of the socio demographics (age, gender, education, working situation, family situation) and disease-related characteristics of the patients (sort of cancer, stage of disease, duration and treatment of cancer); and (3) to examine to what extend participants are satisfied with the intervention.

### Strengths and limitations of the intervention

*Hold on, for each other* is a unique product. This web-based intervention is based on a clear theoretical framework (ACT) and the needs and wishes of the end-users have been carefully taken into account by the use of co-creation. We think that it is this combination that can make *Hold on, for each other* a successful intervention for partners of cancer patients who are in need of support. Also, this intervention is unique because it is positively framed. Partners who participated in our needs assessments agreed that an intervention for partners of cancer patients should be based on a positive approach. According to them, an intervention should be a source of hope and energy and it should focus on things that still can be done, instead of things that no longer can be done (because of their partner’s disease). Therefore, the focus of the intervention is based on the concept of making the best of life in a difficult time.

To the best of our knowledge, *Hold on, for each other* is one of the first web-based interventions for partners of cancer patients. In a literature review only three other web-based interventions for caregivers of cancer patients were found [9]. As we described earlier, the internet and recent technologies offer various possibilities (availability, easy accessible, flexibility) that can be of great value for this target group. Most importantly, partners can do the intervention at any convenient time. Daily exercises are short and can often be done while working, doing the household or giving care.

Another strength of the intervention is that it consists of a variety of components. Partners of cancer patients are offered a package of different features including information, psychological exercises, peer support, practical tips and text messages. Partners can choose freely which of the components they want to use, and in which way they want to use them. For example they can decide if they want to have contact with peers, and if so, they can choose if they want to actively write down their own experiences or if they merely want to read experience of other peers. Also, persuasive elements (such as text messages, tunneling and social support) are incorporated in the design of intervention in order to improve adherence to the intervention [24].

If proven effective, *Hold on, for each other* may easily be implemented in the Dutch healthcare system. One part of our implementation plan is to inform the various stakeholders from the beginning of the project: partners and cancer patients via patient societies (e.g. NFK), the Dutch Cancer Society, health care professionals as physicians, nurses, psychologist, social workers and drop-in centers. We have already started informing the stakeholders in the context of recruitment of participants. If the intervention is found to be effective, we expect that hospitals and other organizations with a focus on psycho-oncology (such as drop-in centers, general practitioners, patient organizations) will be interested in referring partners of cancer patients to this easy accessible psychosocial care option. Health care is rapidly changing and incorporating all kinds of e-health applications. In general, there is a growing interest in web-based, automated screening and monitoring of physical and psychological functioning of patients and partners as part of general portals with different functions (information, electronic dossiers, email, et cetera).

*Hold on, for each other* may also have some limitations. First of all not every partner may be interested in a web-based self-help intervention. We realize that some partners (for example elderly people) might prefer face-to-face contact with a health care professional instead of a (web-based) self-help intervention. However, we believe that the most important step is that partners of cancer patients are at least offered any kind of help. After that, they can decide for themselves if they need help, and whether they would prefer face-to-face contact with a health care professional or whether they would like to participate in a (web-based) self-help intervention. Besides, we think that it doesn’t have to be one or the other. Face-to-face consultation and web-based support can also become more blended, in order to fully utilize the possibilities and advantages of both forms of support. This may also be an appropriate solution for people with severe distress for whom a mere self-help intervention is not sufficient. Highly distressed partners could participate in *Hold on, for each other* under supervision of a health care professional (e.g. a psychologist). The professional could guide them through the intervention and he or she could check on them and constantly monitor on the partners’ (mental) health.

Another limitation may be that the intervention is not targeting bereavement. Therefore, *Hold on, for each other* is not applicable for partners who have already lost their ill spouse.

### Strengths and limitations of the RCT

Our study will answer questions regarding the (cost-)effectiveness of *Hold on, for each other* and possible determinants of the effects of the intervention on psychological distress in partners of cancer patients. We will also conduct a detailed process evaluation to obtain insight in processes in use of the intervention (e.g. time spent on the website, number of exercises completed, content of the messages exchanges). Additionally, satisfaction with the intervention will be measured. For example, participants will be asked if the intervention met their expectations, if they liked the intervention and what they thought about the content of the feedback. These insights can help us to improve the intervention. Furthermore, long-term effects will be studied and an economic evaluation will be done. These two aspects are also highly relevant for a successful implementation in the Dutch healthcare system.

Our study also has some limitations. First, we have no long-term data for the waiting list control condition. For ethical reasons, the participants in this group receive the intervention after the T1 measurement (three months after the baseline measurement). Second, we expect that it is highly challenging to find enough partners of cancer patients who are willing to participate in this trial. From other studies among informal caregivers of cancer patients it is known that it is difficult to find enough participants to meet the previous calculated power (e.g. [55-57]). In order to anticipate on this challenge, we make use of a variety of recruitment channels and recruitment strategies (see Table 3).

To conclude, this study will yield valuable knowledge about the (cost-)effectiveness of a newly developed web-based self-help intervention for partners of cancer patients. If proven to be effective, *Hold on, for each other* may be offered as standard service for partners of cancer patients in the healthcare system.
